### Trial design {8}

The I-FORCE study is a mono-centre RCT with three parallel treatments: (1) SPSP; (2) APT; (3) ST. The patient allocation ratio is 1:1:1. All treatments will provide 50 sessions, the first 32 sessions twice a week (4–5 months), the other 18 sessions weekly (4–5 months). I-FORCE is a pragmatic ecologically valid RCT, which means it will be conducted in the routine specialized clinical setting. Characteristics for a pragmatic trial are the use of minimal exclusion criteria and low barriers to patient participation. Waiving a comparison group with no treatment guarantees inclusion into an effective treatment and minimizes unwillingness to be randomized [35]. This means patients with a wide range of psychiatric comorbidity will be included in this study. Also, use of psychopharmacological medication is not a reason for exclusion.

## Methods: participants, interventions and outcomes

### Study setting {9}

Patients for I-FORCE are recruited from the referrals to the NPI, a Dutch mental health care centre specialized in treatment of PDs. Patients are preselected to the NPI by the central referral department of Arkin after screening for PD and previous treatment. The NPI is a specialist care provider for PD treatment and consists of three locations in Amsterdam (Centre-east, North and West) and one location in Amersfoort. The institute is specialized in both psychodynamic and ST and provides acknowledged clinical training programs for the registration of psychiatrists, clinical psychologists and psychotherapists in the Netherlands.

The treatments of the NPI are organized in three programs: a symptom and coping skills program, a focused personality change program (< 1 year treatment) and a structural personality change program (> 1 year treatment). Within these programs, various treatments are offered. Treatment indication is based on a process of shared decision making. All locations have a longstanding tradition in offering the study treatments SPSP, APT and ST.

### Eligibility criteria {10}^1^

#### Inclusion criteria

In order to be eligible to participate in this study, a patient must meet all of the following criteria:Primary diagnoses: DSM-V diagnosis Cluster-C PD or Otherwise specified PD with predominantly Cluster-C traits, operationalized as a minimum of 5 Cluster-C traits (see Table 2 for examples of Cluster-C traits)Age 18–65 yearsA written informed consentDutch literacyThe willingness and ability to participate in an individual treatment of 50 sessions in 1 year.

**Table 2 Tab2:** Examples of Cluster-C traits

Avoidant PD:	
● Avoids occupational activities that involve significant interpersonal contact because of fears of criticism, disapproval or rejection.	
● Views self as socially inept, personally unappealing, or inferior to others.	
Dependent PD:	
● Needs others to assume responsibility for most major areas of his or her life.	
● Feels uncomfortable or helpless when alone because of exaggerated fears of being unable to care for himself or herself.	
Compulsive PD:	
● Shows perfectionism that interferes with task completion.	
● Is overconscientious, scrupulous, and inflexible about matters of morality, ethics or values (DSM-V, APA, 2013)	

#### Exclusion criteria

A potential subject who meets any of the following criteria will be excluded from participation in this study:(Subthreshold) Cluster-A or B PDHaving received SPSP, APT or ST in the previous yearImmediate intensive treatment or hospitalization is needed, e.g. acute suicidalitySevere psychiatric disorder requiring priority in treatment (autism spectrum disorder, psychotic symptoms/disorder, bipolar disorder, severe substance use disorder)IQ <80. This will be assessed by the recruiting/intakers who carry out the eligibility assessments. When they suspect an IQ < 80 (mental retardation), standard procedure in the NPI is to conduct further diagnostic procedures on intelligence.

#### Therapists

All therapists in this trial are qualified psychologists or psychiatrists with additional training in SPSP, APT or ST for Cluster-C PDs. For ST therapists, a junior registration of the Dutch association of ST is requested (general course in ST and a minimum of 20 supervisions). For APT and SPSP therapists, a general course in APT or SPS is required, and in addition a minimum of 3 months supervision and approval of competence from the supervisor. Next, participating therapists will be trained in the specific Cluster-C protocols prior to the start of the trial. Biweekly peer supervision groups are organized to maintain therapy quality. We expect to include 20 therapists per treatment (SPSP, APT and ST). All therapists will receive a unique code.

## Interventions

### Intervention description {11a}

Patients are randomly assigned to SPSP, APT or ST. All treatments will consist of 50 sessions of 50 min and have a maximum duration of 1 year. The first 32 sessions will be offered twice a week, and after that, therapy will continue once a week (18 sessions).

ST is an integrative treatment approach combining cognitive behavioural, experiential, interpersonal and psychodynamic elements and techniques [105]. The therapy is based on the idea that dysfunctional schemas can develop when core fundamental needs in childhood were not met. It describes pathology in terms of modes; emotional states in which schemas are activated. The goal in ST is to develop a healthy adult mode by reducing dysfunctional coping modes, battling the punitive (self-criticizing) and demanding modes, teaching patients how to meet and be met in their emotional needs that were not met in childhood and processing of adverse childhood experiences, such as abuse and neglect [105]. In ST, use of experiential techniques has a central role in the therapy.

The ST-protocol for Cluster-C personality pathology [5, 6] will be used, except that the first 32 sessions are being offered in a twice instead of once a week frequency and the final sessions (bi)weekly instead of monthly. The protocol starts with a conceptualization phase of 6 sessions. Next, the main treatment phase focuses on experiential techniques (sessions 7 to 32). In the second phase, focus gradually shifts to behavioural change (sessions 33 to 47). The final three sessions are aimed at termination.

At our clinical site (NPI), SPSP, APT and ST are regularly delivered treatment options and supervisors and experienced clinicians are available. Treatment indication is normally performed by the procedure of shared decision making, in which the most suitable treatment (according to the diagnostic team) is presented to the patient, who makes the final choice. New therapists will be trained according to the registration demands of these therapies. In line with recent research showing higher frequency of therapy sessions to be associated with better outcome [18, 22], psychotherapy will be offered twice a week in the first 4-5 months and once a week the second part.

### Criteria for discontinuing or modifying allocated interventions {11b}

Patients can leave the study at any moment for any reason if they wish to do so, with the possibility of finishing the treatment (research dropout). Also, the therapist or the investigator can decide to withdraw a subject from the study for urgent (medical) reasons. Discontinuing treatment is possible in case of a severe psychiatric disorder requiring priority in treatment, deterioration/worsening of the disorder and practical reasons of insufficient commitment/motivation (treatment dropout). It is not possible to switch between different treatments (SPSP, APT and ST) in the trial. If there is a need for further treatment, the patient is offered a regular treatment at the NPI or will be referred.

### Strategies to improve adherence to interventions {11c}

All therapists are attending peer supervision groups at a minimum frequency once every 2 weeks. In every peer supervision group, an adherence attendant is installed to improve adherence to intervention protocols. Regular meetings between the adherence attendants and the researchers take place. In addition, all deviations from the protocol have to be announced and, if necessary, will be discussed in the research committee. The research committee consists of the coordinating researcher, a clinical expert from every treatment (SPSP, APT and ST), a psychiatrist/clinical researcher and a research assistant. They are not among the authors of this protocol. The research committee meets biweekly. Finally, all sessions will be audiotaped and adherence and competence checks will be performed on a selection of the tapes (a random sample of 20% of the treatment sessions).

### Relevant concomitant care permitted or prohibited during the trial {11d}

Care as usual will be delivered considering the prescription of medication. Use and change of medication will be monitored and analysed as a running covariate. Extra health care costs are incorporated in the cost-effectiveness analysis. In view of the long duration of the interventions and the pragmatic design of the trial, some psychotherapeutic co-interventions are allowed with a maximum of 10 sessions and after approval by the research committee. These are as follows: Eye movement desensitization and reprocessing, in case of comorbid post-traumatic stress disorder, booster sessions of motivational interviewing to prevent relapse in substance abuse and family or couples therapy in case of severe relational problems. All these co-interventions are monitored and sensitivity analyses will be done with these variables as covariates.

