### Participant timeline {13}

#### Sample size {14}^3^

First, the required sample size was calculated to compare the three types of active treatments. Three pairwise comparisons will be conducted between the active treatment arms (ST vs. APT, ST vs. SPSP; APT vs. SPSP). We want to detect a medium effect size (*f*=0.11) in a pairwise comparison of pre-post change between two active treatment arms, equivalent to *f*(*v*)=.2460 and Cohen’s *d*=.492, with Bonferroni-corrected *p* = 0.0167, a power of 0.80 and within-person correlation coefficient=0.60, for which 88 patients are needed per arm. Because three types of therapies will be compared, 3 × 88 = 264 participants are needed to perform three pairwise comparisons. We chose a medium effect size (f=0.11^4^) since this would also be a clinically meaningful difference, as opposed to a smaller effect size.

The correlation of 0.60 is an educated guess of the correlation between repeated assessments based on the previous RCTs the authors conducted.

The final analysis will be conducted with mixed regression on time series: the change in slope over time between two treatments. Because power analysis for mixed regression are complex and based on complex assumptions about the covariance-structure, a simplified approach was chosen by conducting a power analysis on the pre-post change.

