## Statistical methods^7^

### Statistical methods for primary and secondary outcomes {20a}

#### Primary study parameter(s)

##### Treatment response: ADP-IV

All analyses will be conducted according to the intention-to-treat principle. Primary and secondary outcomes are analysed with Linear Mixed Models, with random effect of site (if estimation allows). The primary outcome measure is the change in the total ADP-IV score using the dimensional scoring algorithms [86]. Change in the primary outcome measure and the relative effectiveness of the three treatments will be analysed using mixed regression so that all available data are used, and taking into account the levels of participant and time. The addition of random levels for therapist, to adjust for possible therapist effects, will be tested. The underlying distribution of the mixed regression model will be determined based on the distribution of residuals (e.g. normal, gamma, negative binomial). Per-protocol analyses will also be conducted to test for robustness and sensitivity.

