#### Secondary study parameter(s)

##### (Differential) treatment response: secondary study parameters

We will examine change in the secondary outcome measures in the three treatments using mixed regression analysis. The secondary outcome measures include diagnostic status, reliable change and recovery, personality functioning, general functioning, general psychopathology, quality of life and happiness. As the PD severity indices AVPDSI, DPDSI and OCPDS vary per primary PD, they will be first standardized before they are analysed in the complete sample. This analysis will be controlled for primary PS, to account for possible differences in sensitivity to change. The underlying distribution of the mixed regression model will be determined based on the variable type (scale, nominal) and the distribution of residuals (e.g. normal, gamma, negative binomial). In addition, preliminary analyses will test differential treatment retention using survival analysis and mixed logistic regression. Medication confounds will be examined.

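### Medication use after randomisation is to be a running covariate without any restriction; in the effectiveness models this can bias the therapy contrast in either direction

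*Protocol article*

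**What the plan says.** The section on concomitant care {11d} leaves prescribing uncontrolled: "Care as usual will be delivered considering the prescription of medication". The next sentence gives the analysis: "Use and change of medication will be monitored and analysed as a running covariate". A running covariate covering use and change is a time-varying variable measured after randomisation. Nothing restricts it to baseline use or to a secondary role.

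The same section treats psychotherapeutic co-interventions differently: "All these co-interventions are monitored and sensitivity analyses will be done with these variables as covariates".

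Three other places bear on the point:

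- Trial design {8} calls the trial pragmatic and admits medicated patients: "use of psychopharmacological medication is not a reason for exclusion".
- The primary analysis section (Treatment response: ADP-IV) states "All analyses will be conducted according to the intention-to-treat principle". It describes a mixed model with participant and time levels, a random site effect and possibly a therapist level. Medication is neither included nor ruled out.
- The section on secondary study parameters adds "Medication confounds will be examined", without naming a method or model.

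**The concern.** Because prescribing is left to usual care, it can respond to how a patient is doing under the allocated therapy. Medication during follow-up may therefore be a consequence of treatment. Randomisation already balances the causes of medication that exist at baseline, so later medication is not a confounder of the therapy contrast.

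Conditioning on it can do two things. It removes any part of the therapy effect that runs through medication. It can also open a non-causal path between therapy and outcome through unmeasured severity, which drives both prescribing and the ADP-IV score. Either way the coefficient for therapy stops being the total effect of being assigned to one therapy rather than another. That total effect is what an intention-to-treat analysis of a pragmatic trial is meant to deliver.

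At stake is the main comparison of three active therapies, where differences may be modest. Because the wording is unrestricted, a medication-adjusted or an unadjusted model could later be presented as the planned one.

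**Working it through.** **1. The plan's own figure.** The sample size section states "We want to detect a medium effect size (*f*=0.11) in a pairwise comparison of pre-post change between two active treatment arms", with alpha 0.0167, power 0.80, within-person correlation 0.60 and 88 per arm.

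- f(V) = 0.11 × √(2 / (1 − 0.60)) = 0.2460, so d = 2 × 0.2460 = 0.492.
- Noncentral F for the group-by-time term (1 and N − 2 df, λ = f(V)² × N): power is 0.800 at N = 176 and 0.795 at N = 174. So 88 per arm is reproduced.
- d = 0.492 refers to the change score. In units of the SD at one time point it is 0.492 × √(2 × (1 − 0.60)) = 0.492 × 0.894 = 0.44.

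**2. Inputs that the documents do not give.** Medication prevalence, its relation to severity, its effect on outcome and its difference between arms are all absent. Everything below rests on assumed values, and higher scores mean worse outcome.

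**3. Medication as a pure marker of current severity.** Let Y ~ N(−0.44 × arm, 1). Let medication be the top 40% of r × Y + √(1 − r²) × noise, with no effect on Y. Regress Y on arm and medication (large-sample simulation). Residual SD is 1 without the covariate.

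| r | Medicated, by arm | Adjusted effect | Shrinkage | Residual SD | Standardised effect, relative to unadjusted |
|---|---|---|---|---|---|
| 0.3 | 43% v 37% | −0.416 | 6% | 0.97 | 0.97 |
| 0.5 | 44% v 36% | −0.371 | 16% | 0.92 | 0.91 |
| 0.7 | 46% v 34% | −0.306 | 31% | 0.84 | 0.83 |

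The last column uses the adjusted model's own standard error, including the slight loss from correlation between arm and medication. Applied to the planned d: 0.492 × 0.970 = 0.477, 0.492 × 0.914 = 0.450 and 0.492 × 0.826 = 0.406. Power at 88 per arm falls from 0.80 to about 0.77, 0.71 and 0.61 (noncentral F; other approximations differ by about 0.01).

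**4. The same assumption in the plan's pre-post change model** (correlation 0.60). Shrinkage is about 2%, 6% and 12%, and power about 0.78, 0.75 and 0.70. With the baseline score as a covariate instead, shrinkage is about 4%, 11% and 22%. The size depends on the model as well as on the assumed correlation.

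**5. Other structures** (40% medicated in one arm, 30% or 20% in the other):

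- *Shared unmeasured severity, medication without effect on outcome.* With no true difference between therapies, the adjusted contrast is +0.06 SD (40% v 30%) or +0.12 SD (40% v 20%) instead of 0. With a true difference of −0.49 it is −0.43 or −0.37.
- *Medication works (−0.3 SD) and only mediates.* The total effect at 40% v 20% is −0.492 + (−0.3) × (0.20 − 0.40) = −0.432. The adjusted estimate is −0.49, so adjustment enlarges the apparent effect. At 40% v 30%, −0.462 becomes −0.49.
- *Equal medication rates in both arms.* The shift is about 0 in every scenario run.

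**The case against.** The strongest reply is that the document does not place medication in the primary model. The running-covariate sentence stands in the concomitant-care section, the primary analysis section does not name medication, and the note on confounds sits under secondary parameters and may mean only an exploratory check. The statistical section also closes by saying that the analyses are still under development. This stands in part: which analysis carries the covariate is left open, and a reader who inferred that the primary result is certain to be adjusted would go beyond the text. It does not remove the point, because the sentence is unrestricted and its neighbour on co-interventions shows that the authors knew how to restrict one.

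Four stronger readings are tempting and not supported:

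- *The adjustment contradicts intention to treat.* Patients would still be analysed as randomised with all available data. What changes is the quantity estimated.
- *The co-intervention covariates carry the same fault.* They are confined to sensitivity analyses, so the main estimate is untouched. Only their interpretation needs care.
- *A therapy that lowers both symptoms and medication is always penalised.* This holds when medication merely marks severity. When medication works and only mediates, the direction reverses, as step 5 shows. All arms are active therapies at one centre, and a difference in medication between them is possible but not shown.
- *Power could fall to 0.75, 0.63 or 0.44.* Those values follow from step 3 only if the effect is shrunk while the residual SD is held at its unadjusted value. The covariate lowers the residual SD too, so the loss is smaller.

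**Conclusion.** The point holds as a defect in stated wording. Followed literally, the plan conditions the therapy contrast on a variable that therapy can affect, and it describes that variable as a possible confounder, which a post-randomisation variable cannot be for a randomised contrast. The adjusted contrast would then not be the total intention-to-treat effect and could be biased in either direction.

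The bias arises only if therapy affects medication. Neither its size nor its sign can be derived from the documents. The figures of 6% to 31% shrinkage, with power of about 0.77 to 0.61 in place of 0.80, assume 40% medicated, medication as a pure marker of current severity, and a correlation of 0.3 to 0.7. They show that the choice can matter and are not a forecast. In the plan's own change-score model the same assumption gives 2% to 12%.

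This should be fixed before the data are analysed. It does not invalidate the design, and the correction is a free improvement.

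**What to change.** In the concomitant-care section and the analysis section, state that:

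1. The primary and secondary effectiveness models adjust only for variables measured before randomisation. Baseline medication may be one of them.
2. Medication use and change during the trial are reported by arm.
3. Any analysis with time-varying medication is labelled a sensitivity analysis, as the protocol already does for co-interventions, and is read as not estimating the intention-to-treat effect.
4. The sentence on medication confounds is reworded to match.

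The co-intervention sensitivity analyses may stay, with the same caution on how they are read.

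The cost is a few sentences in the protocol and analysis plan. Medication is already monitored, so no new data are needed. Leaving it out of the model does not alter the 88 per arm or the total of 264.

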### Provisions for post-trial care {30}

Patients who drop out from treatments will be referred for regular clinical care. During the follow-up period, no specific interventions are offered. Patients are referred to their general practitioner if clinically necessary. Patients can apply for additional treatment 6 months after treatment termination (18 months after start treatment) with a referral from their general practitioner. In case of additional treatment, patients will not return to the same therapist.

## Outcomes {12}^2^

### Assessment and outcome measures

After the informed consent has been signed, baseline assessment is being conducted. Assessments include computer-based questionnaires and semi-structured interviews. All assessments will be administered in Dutch. To ensure quality of data collection of the semi-structured interviews, all assessors will be trained and supervised. Apart from the outcome measures described below, the demographics and other predictors are being assessed at the baseline measurement. An overview of the instruments at each assessment point is provided in Table 3.

**Table 3 Tab3:**
[figure not shown]
Overview of study design, all instruments and their time of assessment

#### Primary outcome measure

Assessment of DSM-IV Personality Disorders questionnaire (ADP-IV, [87]). The primary outcome is the severity of Cluster-C personality pathology, measured by the ADP-IV. The ADP-IV is a self-report questionnaire, assessing DSM-IV PD criteria. Patients indicate on a 7-point Likert scale to what degree PD criteria hold for them, ranging from 1 (‘not at all’) to 7 (‘completely’), and whether they experience distress from it (on a range from 1—not at all to 3—definitely). Item construction of the ADP-IV allows for both dimensional and categorical diagnostic evaluation [87]. Adequate internal consistency, validity and reliability were shown consistently in previous studies [30, 85].

